##### Secondary outcomes

Secondary outcomes for this study will be the difference between interventions (CRV, OCV) with the additional adjustment for pre-treatment values for the following:
24-h ambulatory brachial diastolic blood pressure24-h ambulatory aortic systolic blood pressure24-h ambulatory aortic diastolic blood pressure24-h ambulatory augmentation indexMean continuous glucose (not adjusting for pre-treatment values)Oxidative stress marker (plasma F_2_-Isoprostanes)Inflammatory markers (serum high sensitivity interleukin-6 and high sensitivity C-reactive protein)

### Data collection, management, and analysis

#### Data collection methods

All measurements, with the exception of glucose monitoring, will be performed at the beginning and end of each 2-week intervention period. Glucose monitoring will be continuous throughout each 2-week intervention period.

##### Blood pressure

Blood pressure will be assessed as 24-h ambulatory blood pressure. Participants will be fitted with an Oscar 2™ Ambulatory Blood Pressure Monitor (ABPM) system (SunTech Medical Inc., Morrisville, NC, USA) by a trained study investigator. Whilst wearing the monitor, blood pressure (brachial and aortic) and heart rate will be measured every 20 min during the day (6 am – 10 pm) and every 30 min overnight (10 pm – 6 am). Use of the monitor will be explained by a trained study investigator, who will also instruct participants to continue daily activities and to avoid any vigorous exercise whilst wearing the monitor. Blood pressure traces that are missing more than 20% of measurements will be excluded from the analyses. If the initial tests are excluded, participants will be encouraged to repeat the test. Participants will use the same blood pressure monitor each time.

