#### Sample size

A sample size of 25 participants completing the trial has been calculated based on the primary outcome of mean 24-h ambulatory systolic blood pressure. To allow for up to 10% withdrawal rate, we plan to recruit 28 eligible participants to this study. We have estimated > 90% retention based on our previous studies [26]. With α = 0.05, 25 participants will provide > 90% power to detect a 2.5 mmHg difference in mean 24-h ambulatory systolic blood pressure. The power calculation is based on an SD of 14 mmHg for systolic blood pressure, a within-period correlation between systolic blood pressure measurements of 0.6, a between period correlation of the mean systolic blood pressure of 0.6, and a minimum of 40 BP measurements over each 24 h period (up to 3 measures each hour 6 am-10 pm and up to 2 each hour 10 pm-6 am) [26]. This calculation utilises the variance inflation factor (VIF) formula for a cross-over trial of VIF=N*(1-ρ)/m, where N is the number of subjects required for a parallel design, ρ is the between period correlation (0.6), and m = 2 is the number of visits per subject [27]. With α = 0.05, 25 participants will also provide > 90% power to detect a 0.30 mmol/l (~ 5%) difference in mean 2-h post-meal estimated blood glucose concentration. This is based on within-group SD of 1.5 mmol/L and a minimum of 80 glucose measures (2 meals per day with soup, for 14 days, with a measure every 15 min over 2 h) over each 2-week period, and a within-subject correlation between measures of r = 0.6.

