#### Outcomes

##### Primary outcome

The primary outcome of this study will be the difference between interventions (CRV, OCV) for 24-h ambulatory brachial systolic blood pressure with the additional adjustment for pre-treatment systolic blood pressure.

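### The trace-validity rule counts only total missing readings, so a recording with as few as 4 of its 16 night readings is kept as a 24-h trace

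*Protocol article*

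**What the plan says.** All references are to the protocol article.

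- **Blood pressure section, schedule.** Blood pressure "will be measured every 20 min during the day", defined as 6 am to 10 pm, and every 30 min from 10 pm to 6 am.
- **Blood pressure section, validity.** "Blood pressure traces that are missing more than 20% of measurements will be excluded from the analyses". No separate minimum is given for day or night. Participants whose initial test is excluded are encouraged to repeat it.
- **Primary outcome section.** The between-intervention difference in "24-h ambulatory brachial systolic blood pressure with the additional adjustment for pre-treatment systolic blood pressure".
- **Sample size section.** The target is stated as "power to detect a 2.5 mmHg difference in mean 24-h ambulatory systolic blood pressure". The calculation counts readings and uses one SD (14 mmHg) and one within-period correlation (0.6) for all of them.
- **Secondary outcomes section.** Brachial diastolic pressure, aortic systolic and diastolic pressure and augmentation index are also 24-h ambulatory measures, taken with the same monitor.

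The article does not say whether the 24-h value is an unweighted or a time-weighted mean, and it gives no day-night difference in systolic pressure.

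**The concern.** The night is one third of the 24 hours but holds only a quarter of the scheduled readings, so it is the window most easily emptied. A rule on the total does not protect it. A monitor taken off for six hours of sleep loses 6 x 2 = 12 night readings, and the recording still counts as a valid 24-h trace although it is almost entirely daytime. If readings are simply averaged, its value is pulled towards the daytime level.

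The primary contrast compares traces from the same person under two soups. Part of the difference could then reflect which readings were lost. That is noise if night loss is similar under both soups, and bias if it is not.

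**Working it through.** **Reading counts (Blood pressure section).** Day: 16 h x 3 = 48. Night: 8 h x 2 = 16. Total: 64.

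**What the 20% rule allows.** 12/64 = 18.75% is kept; 13/64 = 20.3% is excluded. Up to 12 readings may be missing, from any window. If all are night readings, 4 of 16 remain, and 75% of the night is lost.

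**Shift in an unweighted mean.** Let w = night readings / all readings. The shift is (reference weight - w) x (day mean - night mean).

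- Complete trace: w = 16/64 = 0.250.
- Time-weighted reference: 8/24 = 0.333.
- 12 night readings lost: w = 4/52 = 0.077. The shift is 0.173 x the difference against a complete trace and 0.256 x against time weighting.
- 12 day readings lost: w = 16/52 = 0.308. The shift is -0.058 x the difference against a complete trace.

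The day-night difference is an assumption, so a range is shown (mmHg):

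| Assumed day-night difference | 12 night lost, vs complete | 12 night lost, vs time-weighted | 12 day lost, vs complete |
|---|---|---|---|
| 10 | +1.7 | +2.6 | -0.6 |
| 15 | +2.6 | +3.8 | -0.9 |
| 20 | +3.5 | +5.1 | -1.2 |

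This worst-case trace moves by more than 2.5 mmHg only if the difference exceeds 2.5/0.173 = 14.4 mmHg (complete-trace reference) or 2.5/0.256 = 9.75 mmHg (time-weighted reference).

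**Random loss of 12 readings over the 24 h.** The SD of w is sqrt(0.25 x 0.75 x (12/63)/52) = 0.026, so the SD of the shift is 0.39 mmHg at a difference of 15. In 20,000 simulated traces none moved by more than 2.5 mmHg at a difference of 15 or 20.

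**Effect on the group contrast.**

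- Noise. The Sample size inputs give a variance for a 40-reading mean of 196 x (1 + 39 x 0.6)/40 = 119.6 (SD 10.9). With a between-period correlation of 0.6, the within-person variance is 119.6 x 0.4 = 47.8 (SD 6.9). Random loss adds 0.39² = 0.15, about 0.3%. If 20% of all traces were worst-case at a difference of 15, the added variance is 0.2 x 0.8 x 2.6² = 1.1, about 2%.
- Bias. If 20% of traces under one soup only were worst-case at a difference of 15, the contrast moves by 0.2 x 2.6 = 0.5 mmHg, a fifth of the target difference.

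**The case against.** **The averaging method is not stated.** The size of the shift depends on an unweighted mean, and the article never specifies one. The Sample size section works with individual readings and the Statistical methods section names multilevel models, so a reading-level model with a day/night term would be compatible with the text. How readings are averaged may properly be left to a fuller document. This stands, and every figure in mmHg is conditional on it. The validity rule itself is stated, however, and time weighting alone would not cure it: the night third of a valid 24-h mean could still rest on four readings.

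**Unlike quantities.** A reader might infer that the rule lets missing readings move the trial's result by more than the 2.5 mmHg target. The documents do not support this. The target is a group mean difference, whereas the shift is for a single trace with the maximum loss, all at night, and an assumed day-night difference above 14.4 mmHg.

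**Bias is conjectural.** Nothing in the article suggests that night loss differs by soup. The design is a crossover with one schedule and the same monitor each time. This also stands. Against it, participants are not fully blinded, so equal loss cannot be guaranteed.

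**Unequal sampling is not an error in itself.** With complete traces the 75/25 weighting is the same in both periods and creates no spurious difference between soups. Correct.

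**Time weighting has a price.** With a reading-level residual variance of 196 x 0.4 = 78.4, taken as independent, a time-weighted mean of 48 day and 4 night readings has sampling variance 78.4 x ((1/9)/4 + (4/9)/48) = 2.9, against 78.4/52 = 1.5 unweighted. This is a reason to set a night minimum as well as to weight.

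**Conclusion.** The point holds as a weakness in a stated rule. A total-count criterion accepts as a 24-h recording a trace that has lost three quarters of its night readings. If readings are averaged without weights, one such trace shifts by about 1.7 to 3.5 mmHg against a complete trace, or 2.6 to 5.1 mmHg against a time-weighted mean, for assumed day-night differences of 10 to 20 mmHg.

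The effect on the primary contrast is much smaller. It is negligible under random loss, about 2% extra within-person variance if a fifth of all traces were worst-case, and about 0.5 mmHg of bias if that fifth fell under one soup only (both at a difference of 15). The figures rest on an unweighted mean, which is not stated, and on day-night differences that the documents do not give. This is a worthwhile, low-cost improvement. It does not show that the trial's result would be distorted.

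**What to change.** 1. Replace the single total rule with a minimum number of valid readings in each of the day and night windows. One way is to apply the existing 20% limit to each window separately: at most 9 of 48 day readings and 3 of 16 night readings missing (18.75% each). Even an unweighted mean would then be protected. The extreme night weights become 13/61 = 0.213 and 16/55 = 0.291, so a trace shifts by at most 0.041 x the day-night difference against a complete trace, or 0.6 mmHg at 15.
2. Offer the repeat test, already provided for, when either window fails.
3. State the 24-h value before the data are analysed: either (16 x day mean + 8 x night mean)/24, or a model of individual readings with a day/night term.
4. Apply the same rules to brachial diastolic pressure, aortic pressures and augmentation index.

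The cost is a sentence or two and a line of programming. Some traces that now pass would need repeating, and a few might be lost, which matters with 25 completers. Time weighting is somewhat noisier when night readings are few, but a night minimum limits this: with 48 day and 13 night readings the sampling variance is 78.4 x ((1/9)/13 + (4/9)/48) = 1.4, against 78.4/61 = 1.3 unweighted.

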##### Arterial stiffness

Arterial stiffness will be assessed as augmentation index (AIx). AIx is a measure of systemic arterial stiffness that can be derived from aortic waveform data. This data can be obtained using the SphygmoCor component found inside the Oscar 2™ ABPM system (SunTech Medical Inc., Morrisville, NC, USA). The same algorithm as used in the SphygmoCor XCEL is used to obtain the AIx, but in an ambulatory setting instead of resting setting.

##### Glycaemic control

Participants will be fitted with a Flash Glucose Monitoring System (Freestyle Libre; Abbott Diabetes Care Inc., Alameda, CA, USA) for continuous glucose monitoring throughout the intervention periods. This system is comprised of two separate components: a Freestyle Libre sensor and reader. The sensor is small, water-resistant, and disposable, and is worn on the back of the upper arm for up to 14 days. This automatically measures glucose levels in the interstitial fluid every minute using a subcutaneous, wired, enzyme glucose sensing technology [32, 33] and stores data every 15 min for a period of 8 h. Stored glucose data is transferred to the reader by scanning the sensor. The sensor does not require calibration and allows for accurate glucose measurement without the requirement of a finger prick [34]. The screen of the reader will be covered such that participants will remain blinded to their glucose readings throughout the study.

The reader is a compact, handheld device that displays and stores up to 90 days of glucose data. After scanning the sensor, the reader displays a current glucose reading, data for the preceding 8 h (in graph form), and a trend arrow indicating if glucose is increasing, decreasing, or remaining steady. During the study, participants will be asked to scan the sensor at least once every 8 h (morning, afternoon, and evening) during both intervention periods to ensure all glucose data is captured for each 24-h period. Participants will record their diet and the timing of each meal to allow for an accurate measure of post-prandial glucose concentrations.

##### Circulating biomarkers of oxidative stress and inflammation

Fasting (≥12 h) blood samples will be collected at the beginning and end of each intervention period. F_2_-isoprostanes, a biomarker of oxidative stress, will be measured in plasma samples as total (free plus esterified) F_2_-isoprostanes using electron-capture negative-ion gas chromatography-mass spectrometry, as previously described [35]. Serum high sensitivity interleukin-6 (IL-6) and high sensitivity C-reactive protein will be measured as biomarkers of inflammation. Serum high sensitivity IL-6 will be analysed using commercially available ELISA kits, as previously described [36]. Serum high sensitivity C-reactive protein will be analysed using routine laboratory techniques at Fiona Stanley Hospital, Perth, WA. Participants will be asked to refrain from physical activity for 24-h prior to providing a blood sample.

##### Anthropometry

Anthropometric measurements will be used to assess body composition using standard protocols at each pre- and post-intervention visit. These measures will include height, weight, waist and hip circumference, and body fat mass. Participants will be wearing light clothing with no shoes or socks. Height will be measured using a wall-mounted stadiometer to the nearest 1 cm and body weight will be measured with electronic scales to the nearest 0.01 kg. A steel tape measure (W606PM; Lufkin Executive Thinline) will be used to measure waist and hip circumference. Three measurements will be taken for each site and the median of the three values will be reported. Waist circumference (cm) will be measured on bare skin at the narrowest part of the waist. In the case of the narrowest part of the waist not being visible, the waist will be measured mid-way between the lowest rib and the iliac crest. Hip circumference (cm) will be measured at the greatest lateral extension of the hips. Body fat mass will be measured using bioelectrical impedance analysis (Tanita TBF-300 Total Body Composition Analyser) and skinfold measurements. Skinfold callipers will be used to take skinfold measurements at the bicep and tricep sites.

##### Urine, blood, saliva, and oral bacteria collection

Participants will be provided with a sterilized container and instructions to collect a 24-h urine sample which will then be brought back into the clinic. Urine aliquots will be stored at − 80 °C until analysis. Urine creatinine will be measured using routine laboratory techniques at Fiona Stanley Hospital, Perth, WA.

Fasting blood samples will be collected by venepuncture. Total cholesterol, HDL cholesterol, triglycerides, and glucose will be measured using routine laboratory techniques at Fiona Stanley Hospital, Perth, WA. LDL cholesterol will be calculated using the Friedewald formula [37].

Saliva samples will be collected to assess salivary nitrate and nitrite concentrations and the nitrate to nitrite reduction ratio [38]. To obtain the saliva sample, participants will be asked to expectorate into a specimen container while sitting quietly for 5 min. Saliva aliquots will be stored at − 80 °C.

A bacterial sample will be collected from the posterior dorsal surface of the tongue using a sterile stainless-steel metal tongue cleaner. The tongue cleaner will be scraped over the dorsal surface of the tongue until a coating is visible on the tongue cleaner (~ 5 times). This coating will be removed from the tongue cleaner using a sterile collection swab and frozen at − 80 °C for later isolation of DNA.

##### Skin colour assessment

Carotenoid deposition in adipose tissue near the skin affects skin colour and has been found to correlate with fruit and vegetable consumption [39]. This will be measured as previously described [39] before and after each intervention period. Skin colour will be correlated with the Fruit and Vegetable-Specific Food Frequency Questionnaire (FVS-FFQ) and may provide a longer-term marker of fruit and vegetable consumption, and hence compliance throughout the 2-week intervention period. Eight different body sites will be measured: the sole of the foot, shoulder, right cheek, right bicep and tricep, the centre of the forehead, the back of the hand, and the palm of the hand. A Spectro-Guide 4/50 Gloss 6801 spectrophotometer with an 11 mm diameter aperture (BYK Gardner, Maryland, USA) will be used to measure the composition of the light that is reflected back from the skin after exposure to a flash of white light. This will be done three times at each session following calibration of the device according to the manufacturer’s instructions.

##### Questionnaires

Participants will be sent a link via email to complete all study questionnaires online, except for the Cancer Council of Victoria Food Frequency Questionnaire (CCV-FFQ), the FVS-FFQ, and the flavonoids questionnaire, which will be completed at each participant’s first baseline visit under the supervision of a nutritionist. At each participant’s first baseline visit, participants will complete the following questionnaires: 1) demographic and lifestyle questionnaire, a self-administered questionnaire to assess demographic characteristics such as education and previous smoking habits; 2) CCV-FFQ to determine overall habitual dietary intake, a self-administered semi-quantitative dietary questionnaire developed by the Cancer Council of Victoria, Australia [40]; 3) FVS-FFQ to determine habitual fruit and vegetable intake, an interview-based detailed questionnaire to estimate the consumption of fruits and vegetables; 4) flavonoids questionnaire, a self-administered questionnaire to estimate the consumption of foods and beverages rich in flavan-3-ols; 5) beverages questionnaire, a self-administered questionnaire used to estimate average daily/weekly intake of 12 types of beverages (tea, herbal tea, coffee, decaffeinated coffee, chocolate, fruit juice, soft drinks, diet drinks, dairy milk, non-dairy milk, fruit and/or vegetable smoothies, and water) and alcohol (beer, wine, and spirits); 6) the Community Healthy Activities Model Program for Seniors (CHAMPS), used to assess participation (activity type) and energy expenditure (intensity level) of physical activities in older adults [41]; 7) the Longitudinal Aging Study Amsterdam (LASA) questionnaire, a self-administered questionnaire to assess sedentary behaviour of older adults [42]; and 8) Perceived Stress Scale (PSS) questionnaire, a stress assessment instrument compiled of ten questions [43]. The CHAMPS, LASA, and PSS questionnaires will be administered at the beginning and end of each intervention period to monitor any changes in activity and stress levels.

Online questionnaires will be checked for completeness prior to participants coming in for their clinic visits. Participants will be asked to provide any missing information at their visit.

#### Data management

Data collection forms and protocols will be accessible to study investigators in a secured shared drive. Data for questionnaires and clinic visits will be entered electronically by the study coordinator ([name]) and checked by principal investigators ([name] and [name]). Only study investigators ([name], [name], [name]) will be able to access password-protected participant data and all information will remain confidential. To ensure confidentiality, data disseminated to other study investigators will be de-identified. Participant files will be locked and secured outside working hours. Data sent off-site will be de-identified to ensure confidentiality of participants.

#### Statistical methods

Statistical analyses will be performed using IBM SPSS Statistics for Windows, version 25.0 (IBM Corp., Armonk, NY, USA) and STATA, version 16.0 (Statacorp, College Station, TX, USA). Statistical significance will be set at a 2-sided Type 1 error rate of *P* < 0.05. Descriptive statistics of normally distributed continuous variables will be expressed as mean ± standard deviation (SD), non-normally distributed continuous variables as median and interquartile range, and categorical variables as number and proportion (%). The primary analyses will be performed according to a modified intention to treat protocol and will include all randomised participants for which baseline data is obtained. Multilevel models will be used to assess the effect of the dietary interventions and these will produce unbiased estimates of the intervention effects whenever there are small amounts of missing data (i.e. < 10%). Where there is > 10% missing data, multiple imputation will be used as a sensitivity analysis. Covariates will be adjusted for in analyses as necessary. Further exploratory analyses will be conducted on those participants who fully comply to intervention protocols (“per-protocol analyses”).

### Monitoring

#### Data monitoring

The study coordinator ([name]) will oversee all aspects of data monitoring with the assistance of principal investigators ([name] and [name]). Due to the scale and short duration of this trial, a data monitoring committee is not required. We also expect participants will have minimal risks undertaking this trial; therefore, no interim analyses will be conducted.

#### Harms

We expect this trial will have minimal risks to participants. However, if any solicited or spontaneously adverse events or other unintended effects of trial interventions occur, this will be reported by the study coordinator ([name]) to the principal investigators ([name] and [name]) in a prompt manner. The principal investigators ([name] and [name]) will then immediately report the event to the Edith Cowan University Human Research Ethics Committee. The outcome and actions taken will be recorded. Any serious adverse events occurring on site resulting in death will be reported immediately within 24 h and any serious AE occurring on site resulting in other circumstances other than death will be reported immediately within 72 h. All reports will be followed promptly by detailed written reports. The immediate reports and follow-up reports will identify the participant by a unique code number assigned to the trial participant rather than by the participant’s name, personal identification number, and/or addresses.

